**Figure 2 F2:**
[figure not shown]
Overview of psychological assessments. GA, gestational age; MAAS, Maternal Antenatal Attachment Scale; MPAS, Maternal Postnatal Attachment Scale; PAAS, Paternal Antenatal Attachment Scale; PARCA-R, Parent Report of Children’s Abilities-Revised; PCL-5, Post-Traumatic Stress Syndrome Checklist for DSM-5; PPAS, Paternal Postnatal Attachment Scale.

### Phase II: postnatal

After birth, delivery data are recorded, and fresh placentas undergo vascular dye injection followed by histological examination in accordance with the Amsterdam Consensus Criteria.^39^ Neonates receive cerebral ultrasound within 1–3 days to evaluate brain maturation and detect intracranial abnormalities.

### Phase III: follow-up

At 24 months’ corrected age, neurodevelopment is assessed using the Parent Report of Children’s Abilities-Revised (PARCA-R) questionnaire (primary assessment tool) for all children, and (if applicable) Bayley-III/IV testing and neurological examination by trained personnel, according to national neonatal follow-up guidelines.^40^ Severe neurodevelopmental impairment is defined as a PARCA-R or Bayley cognitive or motor score <70, severe neurological dysfunction (any severe motor impairment, including cerebral palsy of at least grade 2 according to the Gross Motor Function Classification System),^41^ or severe visual or hearing impairment, as previously defined.^18^

Parental psychological assessments are repeated at 6 weeks and 24 months postpartum (figure 2, table 3).

**Table 3 T3:** Primary and secondary study parameters

Primary study parameters	
Twin level	GA at sFGR diagnosis.^5^ EFW discordance at diagnosis.^1 43^ UA Doppler abnormalities.^2^ Presence and diameter of AA anastomoses.^22 44^ Oligohydramnios (DVP<2 cm).^45^ Abnormal DV waveform (absent or reversed flow during the a-wave).^46^ Abnormal placental appearance: ultrasound asymmetry between placental shares, with increased thickness and/or heterogeneity of the smaller twin’s placental share.^44^ Major anomalies (EUROCAT criteria).^5 47^ Cord insertion site.^48^

Secondary study parameters	
I. Prenatal	**Fetal ultrasound** Standard ISUOG parameters: UA/MCA/DV PI and waveforms, MCA PSV, EFW (Hadlock 3: HC, AC, FL), amniotic fluid (DVP), bladder and stomach filling, cord insertions.^49^ Additional ultrasound measures as in tables1 2. **Fetal brain MRI** Presence of IVH, PVL, porencephalic cysts, arterial ischaemic infarction, venous infarct (PVHI), intraparenchymal haemorrhage, ventricular dilation, basal ganglia/thalamic injury, cortical injury, cerebellar injury, migration/gyration disorders, or other abnormalities. **Parental well-being** PCL-5^50^, MAAS^51^, PAAS.^52^ **Maternal** Age, pre-pregnancy BMI, smoking status, obstetric history, comorbidities, medication use, recreational drug or alcohol use, educational level (ISCED). **Gestational/fetal baseline** Gravidity, parity, mode of conception, comorbidity during pregnancy, prenatal screening/diagnostics, fetal sex and non-fatal anomalies.
II. Postnatal	**Labour/delivery** Onset of labour, GA at birth, indication for birth, antenatal steroids, magnesium sulphate, mode of delivery, maternal adverse outcomes. **Placenta** Macroscopic and microscopic assessment (Amsterdam Consensus Criteria),^39^ with additional immunohistochemistry if indicated. **Neonates** APGAR at 1, 5, 10 min. Cord blood arterial/venous pH. Birth weight, HC, anthropometrics. Severe neonatal morbidity.^9^ Neonatal mortality (≤28 days). Cranial US: coronal/sagittal planes (anterior/mastoid fontanelles); CC length, cerebellum, pons, BPD; abnormalities and maturation. Brain volume discordance=(ICV large twin–ICV small twin)/ICV large twin×100. **Parental well-being** PCL-5,^50^ MPAS,^53^ PPAS.^53^
III. Follow-up	**Infant neurodevelopment** PARCA-R and/or Bayley-III/IV.^54 55^ **Parental well-being** PCL-5.^50^

AA, artery-to-artery; AC, abdominal circumference; APGAR, Appearance, Pulse, Grimace, Activity, Respiration; BMI, body mass index; BPD, biparietal diameter; DV, ductus venosus; DVP, deepest vertical pocket; EFW, estimated fetal weight; EUROCAT, European Surveillance of Congenital Anomalies; FL, femur length; GA, gestational age; HC, head circumference; ICV, intracranial volume; ISCED, International Standard Classification of Education; ISUOG, International Society of Ultrasound in Obstetrics and Gynecology; IVH, intraventricular hemorrhage; MAAS, Maternal Antenatal Attachment Scale; MCA, middle cerebral artery; MPAS, Maternal Postnatal Attachment Scale; PAAS, Paternal Antenatal Attachment Scale; PARCA-R, Parent Report of Children’s Abilities-Revised; PCL-5, PTSD Checklist for DSM-5; PI, pulsatility index; PSV, peak systolic velocity; PVL, periventricular leucomalacia; sFGR, selective fetal growth restriction; UA, umbilical artery; US, ultrasound.

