### Phase I: prenatal

All participants receive routine clinical care for MCDA twins according to local protocols. In addition, standardised ultrasound measurements such as umbilical venous Doppler flow, cardiac function, assessment of placental structure and fetal brain development are collected at inclusion (T1), 20–22 weeks (T2) and 28–30 weeks’ gestation (T3) (table 1). If inclusion coincides with the second time point (20–22 weeks), only two assessments are performed. A full list of the ultrasound parameters is provided in table 2. Fetal MRI is scheduled at 28–30 weeks’ gestation, currently implemented at selected centres, with ongoing expansion planned across all sites. The acquisition details of the different antenatal images are detailed in table 2. Regular quality audits are performed to monitor imaging, data entry and adherence to study procedures, thereby ensuring consistency and data integrity. Parental psychological well-being is assessed using validated questionnaires at inclusion and at 30 weeks of gestation (figure 2).

**Table 1 T1:** Timing of ultrasound and fetal MRI assessments

GA (weeks)	Standard measurements*	Additional measurements				
		Flow	Placental assessment	Cardiac assessment	Cerebral assessment	Fetal MRI
Inclusion (<28) (T1)	Routine ultrasound (local protocol)	UV: flow and diameter	AA-anastomosis: flow and diameter Placental appearance	CT-ratio In/outflow times TV regurgitation 4C-clip		
20–22 (T2)	Routine ultrasounds (local protocol)	UV: flow and diameter	Placental appearance	CT-ratio In/outflow times TV regurgitation 4C-clip	Still images 3D volume (20–24 weeks)	
22–28	Routine ultrasounds (local protocol)					
28–30 (T3)	Routine ultrasounds (local protocol)	UV: flow and diameter	Placental appearance	CT-ratio In/outflow times TV regurgitation 4C-clip	Still images (28–32 weeks) 3D volume (28+0 weeks)	Fetal MRI (28–30 weeks)
30–delivery	Routine ultrasounds (local protocol)					

* Standard measurements are tailored to local protocol and patient needs.

4C, four-chamber view; CT, cardio-thoracic; 3D, three-dimensional; GA, gestational age; TV, tricuspid valve; UV, umbilical vein.

**Table 2 T2:** Summary of image acquisition

Parameter	Acquisition details*		
Umbilical vein (UV)	Diameter: transverse abdominal section with spine left/right, UV horizontal; measure inner–inner vessel wall edges.	[figure not shown]	[figure not shown]

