### Study outcomes

#### Primary outcome

A composite adverse outcome at the pregnancy level:

Fetal demise of one or both twins (including subsequent demise after a fetal intervention), and/orInduced delivery <32 weeks of gestational age due to perceived fetal distress.

Perceived fetal distress is assessed according to local clinical protocols, as summarised in a recently published multicentre study on outcomes of severe sFGR.^9^ Across centres, fetal indications for earlier delivery commonly include one or more of the following: non-reassuring cardiotocography, significant growth plateau or arrest on the EFW trajectory, worsening Doppler abnormalities such as a reversed a-wave in the ductus venosus, and oligohydramnios. An early onset of sFGR may also contribute to clinical concern.

The candidate predictors (as defined at the time of protocol development) are listed in table 3. The final predictor set will be refined according to the latest literature at the time of analysis.

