### Sample size calculation

Sample size was determined using the four-step approach proposed by Riley *et al*.^42^ Based on the most recent published incidences of intrauterine demise and fetal deterioration in sFGR, we estimated a 23% incidence of the primary composite outcome.^1^ Allowing for five key predictors identified a priori, a minimum of 274 twin pairs with complete data is required to ensure model stability and accurate risk estimation. The full sample size calculation can be found in online supplemental materials.

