### Data analysis plan

The primary analysis will develop a multivariable logistic regression model predicting the composite outcome at diagnosis. Model performance will be evaluated by discrimination (C-statistic) and calibration (scaled Brier score), with internal validation by bootstrapping.

Secondary analyses will include:

Longitudinal modelling of ultrasound trajectories using mixed-effects models (continuous variables) and generalised estimating equations (GEE) (categorical variables), with stratification by gestational age at diagnosis (according to the most recent literature-based cut-offs) and umbilical artery Doppler flow type.Associations between antenatal imaging and placental pathology.Comparison of neurodevelopmental outcomes between co-twins using GEE or paired t-tests.Parental well-being was analysed across timepoints using mixed-effects models.Comparison of outcomes between outpatient- and inpatient-managed pregnancies.

All tests will be two-sided, with p<0.05 considered significant. Analyses will be conducted in SPSS V.25 (IBM, Chicago, USA) and/or R.

Missing data will be minimised through prospective monitoring, regular quality audits and data queries to participating centres. For the primary composite outcome, missing delivery or fetal outcome data will be actively retrieved where possible; pregnancies with unascertainable primary outcomes will be excluded from the primary prediction model analysis. For missing predictor variables, recovery from source imaging or clinical records will be attempted. If data remain missing, appropriate statistical methods will be applied based on the extent and pattern of missingness, in line with best practice for prediction modelling. Missing questionnaire data will be addressed through reminders; incomplete questionnaires will be excluded from the relevant secondary analyses, with the degree of missingness reported.

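### Table 3 codes amniotic fluid for the primary model as a yes/no cut-off (DVP <2 cm), although DVP in cm is itself a listed study measurement

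*Protocol article*

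**What the plan says.** The primary outcome section of the protocol article states: "The candidate predictors (as defined at the time of protocol development) are listed in table 3". In Table 3, under primary study parameters, the amniotic-fluid and ductus venosus (DV) entries read "Oligohydramnios (DVP<2 cm).^45^ Abnormal DV waveform (absent or reversed flow during the a-wave". Among the secondary prenatal parameters the same table lists "UA/MCA/DV PI and waveforms, MCA PSV, EFW (Hadlock 3: HC, AC, FL), amniotic fluid (DVP", so pocket depth is also study data in its own right.

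Other candidates are not cut. Gestational age at diagnosis and discordance in estimated fetal weight carry no threshold, and the artery-to-artery anastomosis entry includes a diameter.

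The data analysis plan says: "The primary analysis will develop a multivariable logistic regression model predicting the composite outcome at diagnosis". On the list itself, the primary outcome section adds: "The final predictor set will be refined according to the latest literature at the time of analysis". The sample size section reads: "Allowing for five key predictors identified a priori, a minimum of 274 twin pairs with complete data is required". Nine candidates are listed, and the article does not say which five are meant. Table 1 places amniotic fluid under routine ultrasound, with the footnote "Standard measurements are tailored to local protocol and patient needs".

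**The concern.** The primary aim is an individual risk estimate at diagnosis. A cut at 2 cm gives one risk to every pregnancy below it and another to every pregnancy above it, so a pocket just over the line is scored like a normal one. If risk varies across the range of DVP, this discards information that the study already holds and lowers discrimination. If few pregnancies fall below 2 cm, the coefficient also rests on a small group and will vary across bootstrap samples. No reason for the cut-off is given beyond one citation.

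**Working it through.** **Inputs from the article.** 274 pairs, 23% incidence and five predictors (sample size section); the 2 cm cut-off and the listing of DVP (Table 3). **Assumptions.** The share of pregnancies below 2 cm, q, is not given and is varied. DVP is taken as normal on a suitable scale, with a log-odds effect that is linear and small.

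**The plan's own figure.** Estimating the overall risk to within 0.05 needs (1.96/0.05)² × 0.23 × 0.77 = 272.1, so 273 pairs against 274 stated. The target reproduces from this step, and the coding of DVP does not enter it. Expected events: 274 × 0.23 = 63.

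**Information kept by a cut-off.** With φ the standard normal density and z_q the point with upper tail q, the share of the linear information kept is φ(z_q)² / [q(1 − q)]. The simulation column is the likelihood-ratio share kept in 1,000,000 simulated pregnancies at 23% incidence, for odds ratios of 1.5 and 2.0 per SD.

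| q (assumed) | Flagged of 274 | Kept, formula | Kept, simulation |
|---|---|---|---|
| 5% | 14 | 22% | 27–29% |
| 10% | 27 | 34% | 39–42% |
| 20% | 55 | 49% | 54–56% |
| 50% | 137 | 64% | 64% |

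The formula peaks at q = 50%, so 64% is its ceiling. The simulation gives somewhat higher shares at low q because the effects simulated are not small.

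**Discrimination of this one predictor.** At an odds ratio of 1.5 per SD, the C-statistic is 0.611 continuous against 0.524, 0.539 and 0.560 for the indicator at q = 5%, 10% and 20%. At 2.0 per SD it is 0.680 against 0.541, 0.568 and 0.602. These are single-predictor values and do not measure the loss in the multivariable model.

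**Counter-case.** If risk steps only at the cut-off (odds ratio 4), a straight-line term keeps just 27% (q = 5%) or 39% (q = 10%) of the indicator's likelihood ratio.

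**Parameter budget.** A linear DVP term uses one parameter, as the indicator does. A 3-knot restricted cubic spline uses two. For the shrinkage criterion (0.9), the required number is proportional to the number of parameters. With an assumed Nagelkerke R² of 0.25, five parameters need 247 pairs and six need 246.9 × 6/5 = 296, which is above 274. The R² used by the sponsor is in a supplement not shown, so this only illustrates that a spline may not fit.

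**The case against.** Five points can be put against this.

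- **The list is provisional, and functional form is usually left to the analysis plan.** This stands in part: nothing is irrevocable, and a secondary listing does not by itself bar DVP from the model. But the refinement clause concerns which predictors enter and promises nothing about coding, and the article itself writes the cut-off into the candidate's definition.
- **Amniotic fluid may not be among the five predictors that enter.** This stands. The point then matters only if it is selected, but a candidate that is coded weakly is also easier to drop.
- **Baseline DVP in cm may be incomplete, since routine measurements follow local protocol.** This is a fair caution about recording. Still, the cut-off cannot be applied without assessing the pocket, and excluding twin-to-twin transfusion at inclusion (Eligibility) already requires judging pockets in both sacs.
- **Risk may really step at the cut-off.** The primary outcome section names oligohydramnios among the common fetal indications for early delivery, and such delivery before 32 weeks is part of the outcome. A step is therefore plausible and the counter-case is real. It is a reason to keep the indicator as a sensitivity model.
- **The same criticism might seem to cover the DV entry.** A reader might infer that it is likewise a cut of DV pulsatility index (PI). The documents do not support this. An absent or reversed a-wave is a qualitative waveform category, so the information formula does not describe it. DV PI would be a different predictor, and the T1 row of Table 1 does not name it.

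**Conclusion.** The point holds for amniotic fluid. Under a smooth relation, the 2 cm cut-off loses information at any prevalence: at least about 36% by the formula, and about 51% to 78% if between 20% and 5% of pregnancies are positive. This rests on a normal measure, a linear log-odds effect and an assumed prevalence.

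A reader might go further and say that the finding is rare and that most of the predictive information is thrown away. The documents give no prevalence and no shape for the risk relation. By the formula, more than half is lost only if risk is smooth and no more than about 20% are flagged. The size of any loss in the full multivariable model is not known. The target of 274 pairs is not called into question. The change is worth making because it bears on the primary aim and costs almost nothing.

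**What to change.** In Table 3, replace the oligohydramnios entry by the smaller twin's DVP at diagnosis, in cm. State that it enters as a continuous term: linear, or a restricted cubic spline with knots fixed in advance if the parameter budget behind the 274 pairs allows it. Keep DVP <2 cm for description and for a sensitivity model, and report how many pregnancies are flagged. Leave the ductus venosus category as it is. DV PI may be examined as an additional or comparison predictor where it is available at inclusion, but should not replace the waveform.

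Cost: a change of wording, plus a check that the cm value is recorded at inclusion in every centre. A linear term needs no extra parameter and a 3-knot spline needs one. Some precision is lost if risk truly steps at 2 cm. Recruitment runs to the end of 2026, so the coding can still be fixed before the analysis.

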### Study outcomes

#### Primary outcome

A composite adverse outcome at the pregnancy level:

Fetal demise of one or both twins (including subsequent demise after a fetal intervention), and/orInduced delivery <32 weeks of gestational age due to perceived fetal distress.

Perceived fetal distress is assessed according to local clinical protocols, as summarised in a recently published multicentre study on outcomes of severe sFGR.^9^ Across centres, fetal indications for earlier delivery commonly include one or more of the following: non-reassuring cardiotocography, significant growth plateau or arrest on the EFW trajectory, worsening Doppler abnormalities such as a reversed a-wave in the ductus venosus, and oligohydramnios. An early onset of sFGR may also contribute to clinical concern.

The candidate predictors (as defined at the time of protocol development) are listed in table 3. The final predictor set will be refined according to the latest literature at the time of analysis.

#### Secondary outcomes

Perinatal morbidity and mortality.Cardiac adaptation in both twins.Fetal brain development and neurodevelopment at 24 months.Correlation between antenatal and postnatal brain imaging.Placental architecture (gross and histological).Impact on parental mental health and attachment.Impact of management protocol differences across centres on primary outcome.

The secondary study parameters are outlined in table 3.

### Sample size calculation

Sample size was determined using the four-step approach proposed by Riley *et al*.^42^ Based on the most recent published incidences of intrauterine demise and fetal deterioration in sFGR, we estimated a 23% incidence of the primary composite outcome.^1^ Allowing for five key predictors identified a priori, a minimum of 274 twin pairs with complete data is required to ensure model stability and accurate risk estimation. The full sample size calculation can be found in online supplemental materials.

### Data analysis plan

The primary analysis will develop a multivariable logistic regression model predicting the composite outcome at diagnosis. Model performance will be evaluated by discrimination (C-statistic) and calibration (scaled Brier score), with internal validation by bootstrapping.

Secondary analyses will include:

Longitudinal modelling of ultrasound trajectories using mixed-effects models (continuous variables) and generalised estimating equations (GEE) (categorical variables), with stratification by gestational age at diagnosis (according to the most recent literature-based cut-offs) and umbilical artery Doppler flow type.Associations between antenatal imaging and placental pathology.Comparison of neurodevelopmental outcomes between co-twins using GEE or paired t-tests.Parental well-being was analysed across timepoints using mixed-effects models.Comparison of outcomes between outpatient- and inpatient-managed pregnancies.

All tests will be two-sided, with p<0.05 considered significant. Analyses will be conducted in SPSS V.25 (IBM, Chicago, USA) and/or R.

Missing data will be minimised through prospective monitoring, regular quality audits and data queries to participating centres. For the primary composite outcome, missing delivery or fetal outcome data will be actively retrieved where possible; pregnancies with unascertainable primary outcomes will be excluded from the primary prediction model analysis. For missing predictor variables, recovery from source imaging or clinical records will be attempted. If data remain missing, appropriate statistical methods will be applied based on the extent and pattern of missingness, in line with best practice for prediction modelling. Missing questionnaire data will be addressed through reminders; incomplete questionnaires will be excluded from the relevant secondary analyses, with the degree of missingness reported.

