## Introduction

 Selective fetal growth restriction (sFGR) complicates approximately 15%–20% of monochorionic diamniotic (MCDA) twin pregnancies and is defined by substantial discordant growth between the twins.^1^ It is associated with high risks of intrauterine death and severe neonatal morbidity in one or both twins.^1^ Management is particularly challenging, as clinicians must weigh the benefits of prolonging gestation against the risks of fetal deterioration, death and morbidity in the co-twin resulting from a very preterm delivery. Although fetal interventions such as selective reduction or cord occlusion may be considered in selected severe cases, no curative treatment exists. As no curative treatment exists, timely delivery to save both twins remains the only intervention, making accurate outcome prediction essential.

Current management is based on the classification of umbilical artery Doppler patterns in the smaller twin (type I to III).^2^ Although associated with distinct prognoses, these patterns can vary considerably during pregnancy and do not represent a progressive severity scale.^2^,^12^ This uncertainty complicates both delivery timing and parental counselling. Improved risk stratification is therefore needed. A severity-based prediction model that integrates ultrasound parameters could better distinguish between mild and severe clinical courses, supporting individualised management, more precise counselling and ultimately improved outcomes.

In addition to improving prediction of the clinical course, it is also important to recognise that the effects of sFGR extend beyond growth itself, with potential consequences for vital organ development and long-term outcomes. Limited evidence suggests cardiac adaptation in both twins, including hypertrophy in the larger twin and impaired ventricular function in the smaller twin, as well as an increased risk of congenital heart disease.^13^,^15^ Neurodevelopmental effects are even less well understood. In singletons with growth restriction, altered brain structure and connectivity have been demonstrated, but systematic evaluation in MCDA twin pregnancies is lacking.^16 17^ Emerging data suggest impaired neurodevelopment in growth-restricted twins,^18^ yet outcomes in single survivors remain largely unknown. The genetically identical co-twin design offers a unique opportunity to study these effects while controlling for genetic and gestational confounders.

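### The plan assigns calibration to the scaled Brier score, an overall accuracy measure that cannot show whether the predicted risks are calibrated

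*Protocol article*

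**What the plan says.** The Data analysis plan of the protocol article describes the primary model in two sentences. The first is "The primary analysis will develop a multivariable logistic regression model predicting the composite outcome at diagnosis". The second is "Model performance will be evaluated by discrimination (C-statistic) and calibration (scaled Brier score), with internal validation by bootstrapping". It pairs each aspect of performance with one measure, and the measure paired with calibration is the scaled Brier score. The article names no calibration slope, calibration intercept, observed-to-expected ratio or calibration plot.

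Two other places show what the model is for. The Introduction expects a severity-based model to help by "supporting individualised management, more precise counselling and ultimately improved outcomes". The Sample size calculation says the target is set "to ensure model stability and accurate risk estimation". Both depend on absolute risks.

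**The concern.** Calibration asks whether pregnancies given a risk of, say, 30% have the outcome about 30% of the time. The scaled Brier score asks how far, on average, predictions lie from outcomes, relative to giving everyone the mean risk. It rises when the model separates cases from non-cases and falls when risks are too extreme, too flat or shifted. A middling value can therefore come from a well-calibrated model with weak predictors or from a badly calibrated model with strong ones.

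This matters because the risks are meant for counselling and management of individual pregnancies. The expected number of events is about 0.23 × 274 = 63, so some overfitting is likely. Overfitting typically makes high risks too high and low risks too low, and a calibration slope and curve are designed to reveal that pattern. The article does not leave the calibration measure open for a later document; it names one, and the one named does not answer the question.

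**Working it through.** **Inputs from the protocol article (Sample size calculation).** Incidence: "we estimated a 23% incidence of the primary composite outcome". Size: "Allowing for five key predictors identified a priori, a minimum of 274 twin pairs with complete data is required". Method: "Sample size was determined using the four-step approach proposed by Riley" and colleagues.

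**Step 1: the plan's own figure.** The four criteria at incidence 0.23 with P = 5 predictors give:

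- Overall risk within ±0.05: (1.96/0.05)² × 0.23 × 0.77 = 272.1, so 273.
- Mean absolute prediction error of 0.05: exp[(−0.508 + 0.259 ln 0.23 + 0.504 ln 5 − ln 0.05)/0.544] = 213.7, so 214.
- Expected shrinkage S = 0.90: P/[(S − 1) ln(1 − R²/S)], with R² the Cox–Snell value. An assumed R² of 0.15 gives 5/[(−0.1) × ln(1 − 0.15/0.9)] = 274.2.
- Optimism in R² of at most 0.05: 133 to 144 pairs for Nagelkerke R² from 0.30 down to 0.10.

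The target of 274 is reproduced to rounding by the third criterion if R² = 0.15, and within 3% by the first. The article does not show the R² it used; for Nagelkerke R² of 0.10, 0.15, 0.20, 0.25 and 0.30 the third criterion gives 657, 430, 316, 247 and 202. The point below does not dispute 274.

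**Step 2: the measure.** Scaled Brier = 1 − Brier/[p(1 − p)], where Brier is the mean of (predicted risk − outcome)². At p = 0.23 the denominator is 0.23 × 0.77 = 0.1771.

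**Step 3: no miscalibration, varying discrimination.** The simulation used 1,000,000 pregnancies, a normally distributed linear predictor and an intercept set for 23% incidence. These are illustrative assumptions. Every model below is perfectly calibrated.

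| SD of linear predictor | C-statistic | Scaled Brier |
|---|---|---|
| 0.4 | 0.610 | 0.027 |
| 0.8 | 0.703 | 0.097 |
| 1.2 | 0.777 | 0.187 |
| 1.6 | 0.830 | 0.276 |

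The score varies tenfold (0.276/0.027 ≈ 10) although calibration is perfect throughout.

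**Step 4: fixed discrimination, varying calibration.** At SD 1.2 (C = 0.78) the linear predictor was stretched and the mean risk held at 23%. Stretching by 1.5 gives a slope of 1/1.5 = 0.67.

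| Calibration slope | 1.0 | 0.8 | 0.67 | 0.5 | 0.33 |
|---|---|---|---|---|---|
| Scaled Brier | 0.189 | 0.183 | 0.170 | 0.133 | 0.059 |

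This is a separate run from Step 3, where the pair for slopes 1.0 and 0.67 was 0.187 and 0.168; the difference between runs is simulation error. In Brier units the Step 3 pair is 0.1771 × (1 − 0.187) = 0.1440 against 0.1771 × (1 − 0.168) = 0.1473. At slope 0.67 the top tenth is predicted at 76.6% and observed at 63.1%, and the lower half is predicted at 5.3% and observed at 9.1%. A gap of 13.5 percentage points at the top of the risk scale costs about 0.02 on the scaled score.

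**Step 5: how likely such a slope is here.** Development samples of 274 pairs at 23% incidence were simulated with five independent, equally strong normal predictors (assumed). In one set of 300 samples per scenario, the mean slope in new data was 0.85 (5th to 95th percentile 0.61 to 1.14) at true C of about 0.70, and 0.91 (0.70 to 1.16) at about 0.78. In another set of 200, the means were 0.87, 0.91 and 0.93 at C of about 0.70, 0.78 and 0.83, with a slope of 0.67 or worse in 10%, 4% and 1.5% of samples. The slope in Step 4 is therefore worse than average for the five-predictor design, but not out of reach.

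**The case against.** The strongest reply has four parts.

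*The score is not blind to calibration.* This stands. It has a calibration component, and with C held fixed it falls as calibration worsens (Step 4). A clearly negative value does signal miscalibration: C = 0.70 with slope 0.33 gives −0.03. A reader might infer that the plan contains no calibration assessment at all, or that no value of the score is informative; both go too far. What remains is that the score barely reacts to moderate miscalibration and never says in which direction the risks err.

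*The C-statistic is reported beside it, and both are bootstrapped.* This stands in part. Because C is shown, the fair comparison is at equal C, which is why the figure relied on is 0.19 against 0.17. Optimism correction would also register overfitting: in the five-predictor simulation at C of about 0.78, the score fell from 0.208 apparent to 0.167 in new data. The corrected value is still one mixed number. It does not tell extreme risks from weak predictors, nor locate the error.

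*The 77% against 63% example is a tail case.* This stands. At slope 0.9, nearer the average for five predictors, the top tenth is predicted at about 67% against 63%, and the lower half at 8% against 9%. The example shows what the score can miss, not what to expect.

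*A condensed article leaves such detail to the analysis plan.* This would answer a complaint that a plot or slope is merely unmentioned. It does not answer a sentence that names the wrong measure. An unseen document may add the right ones, and the article sets no score threshold for declaring good calibration, so the consequence is a possibility and not a certainty.

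**Conclusion.** The point holds in this form: the article assigns calibration to an overall accuracy measure, so the performance assessment as written cannot show whether the predicted risks are calibrated. At 23% incidence the score runs from about 0.03 to 0.28 with no miscalibration, while a slope of 0.67 at C = 0.78 moves it by only about 0.02. The figures rest on a normal linear predictor and chosen slopes, which are illustrative assumptions. The mixing of discrimination and calibration follows from the definition of the score and does not depend on them.

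Three further inferences are not supported. The Sample size calculation is not in error on this point; its reference to accurate risk estimation states an aim and contradicts nothing. Coefficient shrinkage, or a comparison with a model using umbilical artery Doppler type alone, may be worth having, but their absence does not follow from the mislabelled measure. Nor do the documents show that a miscalibrated model will be reported as calibrated, only that the named measures could let one pass unnoticed.

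**What to change.** In the Data analysis plan, replace the calibration item in the sentence on model performance so that it reads: *calibration (bootstrap optimism-corrected calibration slope and intercept, and a smoothed calibration curve) and overall performance (scaled Brier score)*. The C-statistic and the bootstrap stay as planned.

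The target stays at 274 pairs. The added measures come from the same fitted model and the same bootstrap, so the cost is one sentence and a few lines of code, with no extra data and no burden on participants. Recruitment runs to the end of 2026, so the wording can be settled before the primary analysis.
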